## Abstract

**Background:**

Parents typically do not recognise their child’s weight status accurately according to clinical criteria, and thus may not take appropriate action if their child is overweight. We developed a novel visual intervention designed to improve parental perceptions of child weight status according to clinical criteria for children aged 4–5 and 10–11 years. The Map Me intervention comprises age- and sex-specific body image scales of known body mass index and supporting information about the health risks of childhood overweight.

**Design:**

This cluster randomised trial will test the effectiveness of the Map Me intervention. Primary schools will be randomised to: paper-based Map Me; web-based Map Me; no information (control). Parents of reception (4–5 years) and year 6 (10–11 years) children attending the schools will be recruited. The study will work with the National Child Measurement Programme which measures the height and weight of these year groups and provides feedback to parents about their child’s weight status. Before receiving the feedback, parents will complete a questionnaire which includes assessment of their perception of their child’s weight status and knowledge of the health consequences of childhood overweight. The control group will provide pre-intervention data with assessment soon after recruitment; the intervention groups will provide post-intervention data after access to Map Me for one month. The study will subsequently obtain the child height and weight measurements from the National Child Measurement Programme. Families will be followed-up by the study team at 12 months. The primary outcome is any difference in accuracy in parental perception of child weight status between pre-intervention and post-intervention at one month. The secondary outcomes include differences in parent knowledge, intention to change lifestyle behaviours and/or seek advice or support, perceived control, action planning, coping planning, and child weight status at 12 month follow-up.

**Discussion:**

The Map Me tool has potential to make a positive impact on children’s health at a population level by introducing it into current intervention programmes to improve accuracy of parental perception of child’s weight status. This trial will inform the action of researchers, educators, health professionals and policy makers.

**Trial registration:**

Current Controlled Trials ISRCTN91136472. Registered 3 May 2013

## Background

The prevalence of overweight and obesity in childhood is a public health concern for the United Kingdom [1]. To effectively combat this problem, the emphasis needs to be placed on population-wide prevention in a range of settings including the home environment [1]. Parents play an important role in shaping children’s health related behaviours [2] and are relied upon to recognise unhealthy weight gain and take the necessary action [3]. However, there is a growing evidence base demonstrating that parents of overweight and obese children typically do not describe their child as such [3–7].

Data on how parents’ perceptions of their child’s weight status can be improved are limited. The National Child Measurement Programme (NCMP) currently measures height and weight of school children in reception (age 4–5 years) and year 6 (age 10–11 years) in maintained schools, that is all but special needs and fee-paying schools, in England. These data are used to calculate each child’s body mass index (BMI): an index of overall body fat based on height and weight (BMI = weight[kg]/height^2^[m]). The BMI scores are converted to age and sex specific centiles calculated using the British 1990 growth reference UK90 [8] to determine the number of children defined as underweight, healthy weight, overweight or obese as a proportion of the number measured. Children are classified as ‘underweight’ if they have a BMI below the 2^nd^ centile; as ‘healthy weight’ between the 2^nd^ and 90^th^ centiles; as ‘overweight’ between 91^st^ and 97^th^ centiles; and as ‘very overweight’ at or above the 98^th^ centile. These results are typically communicated to parents within six weeks of measurement by letter which informs them of their child’s BMI and the UK90 category into which this falls, usually with a Change4Life leaflet (a public health programme to tackle obesity in England, and run by the Department of Health) and information on local services. Evaluations of the letters indicate that they are often not well received by parents of overweight children who doubt the veracity of the assessments, and therefore may fail to promote appropriate action [9, 10]. Similarly, the growth chart is regularly used to monitor children’s growth and to educate families about the growth process. However, the usefulness of these charts depends on whether parents are able to understand them and existing evidence shows that the general population does not [11]. Other approaches may therefore be more effective than teaching parents mathematical concepts [12].

Parents do use subjective approaches to evaluate their child’s weight status [5]. They report making visual comparisons within peer groups and tend to rely on extreme cases as a reference point [6]. As the population becomes increasingly overweight, an upward shift in the threshold for perception of child overweight may have occurred [13]. When parents are asked to classify their child’s weight status, BMI is a significant predictor, but visual representations of body fatness such as skinfolds and waist circumference contribute most to their responses [14]. Given parents’ reliance on visual characteristics [6, 14], it may prove beneficial to use visual images of child weight status to improve parents’ identification of overweight in their children. Some research has explored parental perceptions of child weight status using visual images [15–18], but the methods used are limited because they are not usually based on BMI. Even those that are based on BMI are limited. For example, the Children's Body Image Scale consists of photographic figures of pre-pubescent children, seven each of boys and girls [19]. The children range from very thin to obese and each figure corresponds to a known BMI range covering the 3rd to 97th BMI percentiles for 10-year-old children based on United States’s standards, the National Center for Health Statistics [20]. None exist which include the full range of BMI measured in English children and correspond to commonly used UK90 [21] criteria for overweight in England.

Once parents recognise that their child is overweight, parents can play a positive role in the further development of their child’s weight in two ways: they can either seek external support for weight control (such as those provided by local services), and/or they can take action at home by changing aspects of their child’s diet, time spent in sedentary or physical activities. Previous research has explored factors associated with parents’ readiness to modify the lifestyle of their overweight child; parents’ perception that their child’s weight was a health problem was associated with an increased likelihood of them implementing lifestyle changes [2]. Providing parents with information about the health risks and consequences of childhood overweight to encourage positive changes in their child’s life should, therefore, be beneficial. However, recognition and knowledge alone do not guarantee action. There is considerable evidence showing that social cognitions, such as those postulated by the Theory of Planned Behaviour [22] and Social Cognitive Theory [23], are important predictors of health-related behaviours. Both theories emphasise the key role of intentions to act or behavioural goals and of self-efficacy (the perceived capability of performing the target behaviour), for example, the ability to make a difference to the child’s weight. In addition to knowledge, intentions and goals are also a reflection of the attitudes people hold towards the behaviour (evaluation of favourableness based on specific expected outcomes) and the subjective norm. While these social cognitions are predictive of health-related behaviour [24] there is increasing recognition that people do not always act in accordance with their intentions and beliefs. This phenomenon has been called the intention-behaviour gap [25]. To bridge this gap, more recent theories such as the Health Action Process Approach [26] incorporate additional, self-regulatory constructs, such as action planning and coping planning which have improved the prediction of behaviour [27]. By specifying when, where and how to act (action planning) and how to respond to certain obstacles and barriers to action (coping planning), individuals become more likely to enact their intentions [28–30].

This trial will measure parental perception of their child’s weight status, knowledge of the consequences of a child being overweight and intention to change lifestyle behaviours and/or seek advice. Intention will be assessed by items defined by the Target, Action, Context and Time principle [31]. The study will also measure predictors of behaviour change in parents including: perceived control over child’s behaviour and self-efficacy defined as the parent's confidence in performing a behaviour [32, 33]; action planning [32, 34]; coping planning, a barrier-focused strategy to avoid unwanted responses to situational demands or social pressure [35] and measures of parent-reported behaviours aimed at seeking support and facilitating weight control in their children [36].

The aim of the trial is to test whether, compared to controls, providing the Map Me intervention [37] to parents:increases the proportion of parents accurately assessing their child’s weight status (convergent with the UK90 criteria [21])increases parental knowledge of the consequences of their child being overweightimproves parental intention to take action, perceived control over child’s behaviour and self-efficacy, action planning and coping planningis associated with weight status outcomes in children at 12 month follow up

Additionally, differences in the effects of using the web-based and paper-based formats will be investigated.

## Methods

### Study design

A three arm cluster randomised trial with primary schools as the unit of randomisation will be conducted with a minimum of 36 schools. It will test two versions of the intervention against the control group (Fig. 1). The intervention period is four weeks, and follow-up is 12 months.

**Fig. 1 Fig1:**
[figure not shown]
Study design

### Intervention

This research team has developed visual age and sex-specific body images scales; there are four scales (girls 4–5 years; boys 4–5 years; girls 10–11 years; boys 10–11 years). Each scale consists of images of body shapes of known BMI ranging from underweight to very overweight in the following categories: underweight; lower healthy weight; mid healthy weight; upper healthy weight; overweight; very overweight (clinically obese); very overweight (extremely obese). Supporting information was also developed about the health risks of childhood overweight, healthy lifestyle behaviours and sources of support and advice (for example: general practitioner or school nurse; National Health Services (NHS); weight management programmes for children). The body image scales and supporting information are combined to form an intervention called ‘Map Me’. Map Me has been developed in two formats:

#### Intervention A

A parent information pack containing a paper-based version of Map Me appropriate to their child (i.e. age and sex specific).

#### Intervention B

A parent information pack with the website address and login details for the web-based version of Map Me.

Depending on randomisation, parents in the intervention groups will have *either* the opportunity to read the paper-based Map Me which includes body image scales with the weight status of each image indicated (for example, underweight, healthy weight, overweight) *or* access to an interactive web based tool utilising the body image scales with facility for the parent to choose the body image they think best represents their child, this image will then shrink or expand to the correct representation when the child’s height and weight are imputed, and a facility which will allow the child’s correct body image to be projected forward to predict their future adult body image assuming their current weight status tracks into adulthood. In this method of delivery, appropriate feedback on their child’s BMI is given. Both methods provide information about the consequences of childhood overweight. The development of Map Me will be published in full in a separate paper.

### Procedure

Within schools, all the parents of 4–5 and 10–11 year old children will be sent an invitation to join the study. Recruited parents will be those who return a signed consent form. Every school that has at least one consented child will be randomised to Intervention A, Intervention B or control using a 1:1:1 ratio, as described in the ‘randomisation of schools’ section.

Parents in the control group will provide the baseline data for the trial. They will not receive either intervention during the study period. They will be posted the study questionnaire soon after the study team receive their consent forms; the questionnaire consists of the outcome and explanatory measures. Parents in the intervention groups will receive the intervention by post. Those randomly assigned to the web-based version will additionally receive a follow-up email with website link, if an email address was obtained. The intervention period lasts four weeks and after this period has elapsed all parents in the intervention groups will be posted the study questionnaire. Parents will be asked to complete and return the questionnaire to the study office in the provided postage-paid envelope. In the majority of cases, the study team will obtain the child height and weight measurements from the NCMP. All parents and children will be followed up at 12 months after the first day of the intervention; parents will be sent the study questionnaire to complete and return to the study office, and the children will be measured for height and weight by the study team, usually at school.

A favourable ethical opinion was obtained from National Research Ethics Service, Committee North East - Newcastle and North Tyneside 2: reference 12/NE/0409.

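### Controls answer the primary questionnaire about four weeks earlier than the intervention arms, so elapsed time and early loss are aligned with arm

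*Protocol article*

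**What the plan says.** The protocol article gives the timing of the first questionnaire twice, and the two accounts agree.

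- **Controls.** Procedure: "They will be posted the study questionnaire soon after the study team receive their consent forms". Abstract, Design: "The control group will provide pre-intervention data with assessment soon after recruitment".
- **Intervention arms.** Procedure: "The intervention period lasts four weeks and after this period has elapsed all parents in the intervention groups will be posted the study questionnaire". Abstract, Design: "the intervention groups will provide post-intervention data after access to Map Me for one month".

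The control answers double as the trial's starting point: "Parents in the control group will provide the baseline data for the trial". The abstract defines the primary outcome as "any difference in accuracy in parental perception of child weight status between pre-intervention and post-intervention at one month". Since the two time points come from different parents, this is a between-arm contrast. The Statistical analysis section tests it that way, as a difference in proportions between control and intervention groups.

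The Sample size section places the powered difference, control against each intervention group, at one month.

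The abstract also states that parents complete the questionnaire before they receive NCMP feedback, and makes no exception by arm. For the later visit the Procedure says: "All parents and children will be followed up at 12 months after the first day of the intervention".

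**The concern.** Randomisation makes the schools comparable at allocation. The mailing schedule then introduces a difference after allocation: one arm is measured near week 0 and the other two at week 4 or later. Two things differ between arms besides Map Me.

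- **Elapsed time.** Anything that alters how parents see their child's weight over about four weeks, including simply being in a study about child weight, acts longer on intervention parents before they answer.
- **Opportunity for loss.** Intervention parents have about four more weeks in which to lose interest or leave. If those who stay perceive weight more accurately, or less accurately, than those who go, the observed proportion shifts with no true effect.

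The multilevel model cannot separate either from the intervention effect. The covariates listed are deprivation, free school meals and anthropometry, while assessment time is almost a function of arm. The analysis section speaks of change in perception, but the Procedure describes no earlier perception measure in the intervention arms from which change could be taken. At stake are the primary outcome and the questionnaire-based secondary outcomes taken at the same time.

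**Working it through.** **1. Passages side by side**

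| Item | Control | Intervention A and B |
|---|---|---|
| First questionnaire posted (Procedure) | soon after consent form received | after four-week period has ended |
| Status of data (Abstract) | pre-intervention | post-intervention |
| Powered contrast (Sample size) | one month | one month |
| Questionnaire before NCMP feedback (Abstract) | yes | yes |

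The first and third rows disagree for controls. The fourth row shows no difference by arm.

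**2. The plan's own sample size**

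Inputs from Sample size: 30% versus 50%, type 1 error 2.5%, power 90%, Fleiss's method with continuity correction, intra-cluster correlation 0.01, cluster size 15. Sidedness is not stated; two-sided reproduces the figure.

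- Uncorrected: n' = [2.241 × √(2 × 0.4 × 0.6) + 1.282 × √(0.21 + 0.25)]² / 0.20² = 146.7, that is 147.
- Corrected: n = (n'/4) × [1 + √(1 + 4/(n' × 0.20))]² = 156.5, that is 157 per group.
- 3 × 157 = 471; 471 × 1.14 = 536.9, that is 537; 537/15 = 35.8, that is 36 schools.

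All stated figures reproduce. The calculation already assumes a contrast at one month, so equal timing changes nothing here. The issue is bias, not sample size.

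**3. Illustration of drift (assumed; the documents give no figure)**

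Twelve schools per arm × 15 children = 180; 180/1.14 = 157.9 effective per arm. Suppose there is no true effect, 30% are correct in controls, and 30% + d in an intervention arm from elapsed time alone. With a two-sided 2.5% normal test (critical value 2.241), the rejection rate is the two-tail probability, using the pooled standard error for the cut-off and the unpooled one for the distribution.

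For d = 5 points: pooled SE = √(2 × 0.325 × 0.675/157.9) = 0.0527; unpooled SE = √((0.21 + 0.2275)/157.9) = 0.0526. Upper tail beyond (0.1182 − 0.05)/0.0526 = 1.29 is about 0.098; the lower tail is below 0.001.

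| Assumed shift d (points) | Type I error per comparison |
|---|---|
| 0 | 2.5% |
| 2 | 3.6% |
| 3 | 5.0% |
| 5 | 9.8% |

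**4. Illustration of selective loss (assumed)**

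If correct perceivers are r times as likely as others to stay through the extra weeks, a true 30% is observed as 0.3r/(0.3r + 0.7).

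- r = 1.0: 30.0%
- r = 1.1: 0.33/1.03 = 32.0%
- r = 1.2: 0.36/1.06 = 34.0%

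With r below 1 the shift goes the other way; r = 0.9 gives 0.27/0.97 = 27.8%. The only retention figure in the document is 75% at 12 months, not split by arm, so r cannot be estimated.

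**The case against.** The strongest counter-argument concerns NCMP feedback. A reader might infer that the intervention arms answer after the feedback letter and controls before it, so that a positive result could be the letter at work. The documents do not support this. The abstract puts the questionnaire before feedback for all parents, and School sample has regions chosen with knowledge of the NCMP schedule, which is consistent with protecting that order.

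Nor does the timing of the letter prove otherwise. Background says "These results are typically communicated to parents within six weeks of measurement by letter", but that clock starts at the child's measurement, and no section ties the measurement date to consent or to dispatch of Map Me. This objection stands. What is left is an execution risk: a return that comes in late may follow the letter, and this is likelier where the questionnaire goes out four weeks later.

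A second objection is that every bias figure is assumed. That also stands. Zero drift and no selective loss are compatible with the documents, and four weeks is a short time.

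A third is that the schedule is deliberate and openly described. That is true, but openness does not remove the alignment of time with arm, and the Sample size section describes a different contrast.

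The 12-month anchor is a lesser matter. Controls have no first day of intervention, but a shared calendar date is a workable reading, and the gap at 12 months would be a matter of weeks.

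**Conclusion.** The point holds in a limited form. Controls and intervention parents are assessed about four weeks apart for the primary outcome, the Sample size section assumes both are assessed at one month, and no intervention-arm baseline is described that could correct for the difference. The figure of about four weeks assumes that Map Me is dispatched about as promptly as the control questionnaire.

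The documents give neither the size nor the direction of any resulting bias. The illustrations show sensitivity, not an estimate: an unrelated rise of 3 points, small beside the 20-point target, would double the type I error per comparison from 2.5% to 5%, and 5 points would bring it to about 10%.

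It would go too far to say that NCMP feedback is confounded with arm, or that the comparison is known to be biased. The change is worth making because it removes a design-induced difference from the primary contrast at little cost.

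**What to change.** - Post the first questionnaire to all three arms at the same interval, four weeks after allocation or dispatch of Map Me, and still before NCMP feedback. If dispatch is the reference, give control schools a matching date. This also brings the Procedure into line with the Sample size section.
- Anchor the 12-month follow-up to a date that exists in every arm, such as allocation.
- Record the questionnaire completion date and the NCMP letter date for each family, so that returns after the letter can be counted by arm.

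**Cost.** The sample size stays at 157 per group, 537 in total and 36 schools. The main change is a mailing date, plus two dates to record. Control returns may fall slightly after a four-week wait. Controls would be assessed closer to the NCMP letter, so the order of questionnaire and feedback needs watching in all arms. Control data could no longer be called pre-intervention data, and the abstract's definition of the primary outcome would need rewording as a between-arm difference at one month.

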### School sample

Schools will be drawn from Local Education Authorities (LEA) regions in England. Regions will be selected by the study team based on knowledge of the schedule of the NCMP. Special needs and fee-paying schools will be ineligible for inclusion in the trial, to align with the NCMP mandated in LEA-maintained schools only. The body image scales included in the Map Me tool were developed using a primarily Caucasian sample of children; therefore schools with over 35 % Black and Minority Ethnic population will not be included. All other schools will be invited and those agreeable will be enrolled to the study. In some cases local authorities may offer to send the study invitation letters directly to parents, eliminating the need to enrol the school.

